#### ***Serious Adverse events (SAEs)***

A serious adverse event is any untoward medical occurrence or effect that

- results in death;
- is life threatening (at the time of the event);
- requires hospitalisation or prolongation of existing inpatients' hospitalisation, admittance to the Intensive Care Unit due to respiratory insufficiency will not be reported as an SAE;
- results in persistent or significant disability or incapacity;
- is a congenital anomaly or birth defect; or
- any other important medical event that did not result in any of the outcomes listed above due to medical or surgical intervention but could have been based upon appropriate judgement by the investigator.

The investigator in a participating center will report all SAEs to the coordinating investigator without undue delay after obtaining knowledge of the events.

The sponsor will report the SAEs through the web portal *ToetsingOnline* to the accredited METC that approved the protocol, within 7 days of first knowledge for SAEs that result in death or are life threatening followed by a period of maximum of 8 days to complete the initial preliminary report. All other SAEs will be reported within a period of maximum 15 days after the sponsor has first knowledge of the serious adverse events.

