### 3. Subject population

#### 3.1 Number of subjects and subject selection

Fourty patients will be randomized 1:1 for the intervention with lanadelumab iv. Twenty SARS-COV2 positive patients treated with lanadelumab 300 mg IV on day 1, followed by a second dose of lanadelumab 300 mg IV on day 4. The other 20 lanadelumab patients will receive the same treatment algorithm while NOT receiving lanadelumab. The estimated number of patients being treated for COVID disease is difficult to predict. Currently about 20% of the COVID-19 patients are hospitalized and out of these patients about 20% is admitted to the ICU.

These will be patients from the following centers:

- Amsterdam UMC, Amsterdam
- Radboud University Medical center, Nijmegen,
- University Medical Center Utrecht, Utrecht,
- Rijnstate Hospital, Arnhem
- Flevoziekenhuis, Almere

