### **3.7 Stopping rules for the study**

The study will be stopped if at least 1 patient experiences a severe adverse event that is attributable to lanadelumab treatment and evaluation will take place before the next subject is treated or whether the second dose of lanadelumab can be given. A semi-sequential design will be deployed. This means that we will start with a single individual to be entered into the study. A second subject can enter the study 24 hours after the first subject has started. After the second participant has received the first dose without severe complications, the 3rd to 5th participant may be recruited.

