#### ***Adverse events (AEs)***

Adverse events are defined as any undesirable experience occurring to a subject during the study, whether or not considered related to the investigational product. All adverse events reported spontaneously by the subject or observed by the investigator or his staff will be recorded, meeting all of the following criteria:

- **Severity: Grade 2 or higher, or grade 1 lasting longer than 1 week, graded by the CTCAE (Common Terminology Criteria for Adverse Events, v5.0).**
- **Causality: there needs to be a reasonable suspicion of the AE being an effect of the study medication.**

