***Suspected unexpected serious adverse reactions (SUSARs)***

Adverse reactions are all untoward and unintended responses to an investigational product related to any dose administered.

Unexpected adverse reactions are SUSARs if the following three conditions are met:

1. the event must be serious;
2. there must be a certain degree of probability that the event is a harmful and an undesirable reaction to the medicinal product under investigation, regardless of the administered dose;
3. the adverse reaction must be unexpected, that is to say, the nature and severity of the adverse reaction are not in agreement with the product information as recorded in:
  - Summary of Product Characteristics (SPC) for an authorised medicinal product;
  - Investigator's Brochure for an unauthorised medicinal product.

The investigator in a participating centre will report the SUSAR to the coordinating investigator.

The coordinating investigator will report expedited the following SUSARs through the web portal *ToetsingOnline* to the METC:

- SUSARs that have arisen in the clinical trial that was assessed by the METC;
- SUSARs that have arisen in other clinical trials of the same sponsor and with the same medicinal product, and that could have consequences for the safety of the subjects involved in the clinical trial that was assessed by the METC.

The remaining SUSARs are recorded in an overview list (line-listing) that will be submitted once every half year to the METC. This line-listing provides an overview of all SUSARs from the study medicine, accompanied by a brief report highlighting the main points of concern.

The expedited reporting of SUSARs through the web portal Eudravigilance or ToetsingOnline is sufficient as notification to the competent authority.

The sponsor will report expedited all SUSARs to the competent authorities in other Member States, according to the requirements of the Member States.

The expedited reporting will occur not later than 15 days after the sponsor has first knowledge of the adverse reactions. For fatal or life threatening cases the term will be maximal 7 days for a preliminary report with another 8 days for completion of the report.

**For individual sites, the local investigator completes the SAE report in Castor and providing as much detailed information as known and relevant to the event within 24 hours of discovery of the event.**

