#### 9.1.4 *Benefits and risks assessment, group relatedness*

For a number of reasons administration of the intravenous lanadelumab can lead to problems with administration. Pharmacokinetic properties and information about safety have only been derived from modelling and simulation.

There are currently no treatment options for patients with COVID19. As lanadelumab subcutaneous is expected to result in a substantial delay in effect due to the slow absorption, intravenous administration is important. Therefore, we want to investigate this alternative safe method to administer lanadelumab. The potential value of this research is to provide both the proof of concept as well as safety of treatment in COVID disease..

This study will be performed in patients with COVID disease as recommended by the guidelines for bioequivalence. Lanadelumab is well tolerated in other patient cohorts. There is a mild side effect profile as also

demonstrated in large phase III trials. Moreover, to limit the risk of side effects, this study is designed as two dose study.

The study participants are subjects  $\geq 18$  years. The safety and efficacy of intravenous lanadelumab in children and adolescents aged less than 18 years have not yet been established.

For pharmacokinetic purposes and safety assessment, blood samples will be collected. The total blood volume taken will be approximately 100-150 mL. During the days that blood samples will be collected for biomarker and PK-information, an intravenous cannula will be inserted to facilitate blood sampling and limit the amount of venous punctures.

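### The SAE waiver for ICU admission with respiratory insufficiency has no exception for suspected drug relation, so a serious reaction to IV lanadelumab could be notified late

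*Protocol*

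**What the plan says.** In the protocol's section 6.3, under Serious Adverse events, the criterion on hospitalisation or its prolongation ends with the clause "admittance to the Intensive Care Unit due to respiratory insufficiency will not be reported as an SAE". No condition is set on suspected cause, timing after an infusion, or treatment arm. The other criteria in the list (death, life-threatening event, disability, congenital anomaly, other important medical event) carry no such waiver.

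The provisions around the clause are these:

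- **Ordinary adverse events (6.3).** An event is recorded if it meets a severity threshold (grade 2 or higher, or grade 1 lasting more than a week) and a second condition: "Causality: there needs to be a reasonable suspicion of the AE being an effect of the study medication". No expedited route is given.
- **SUSARs (6.3).** The first of three conditions is that "the event must be serious".
- **Site reporting (6.3).** The local investigator completes an SAE report in Castor within 24 hours of discovery. That report triggers an automatic e-mail to the coordinating investigator.
- **Stopping rule (3.7).** "The study will be stopped if at least 1 patient experiences a severe adverse event that is attributable to lanadelumab treatment", with evaluation before the next subject is treated or the second dose is given. On staggering: "A second subject can enter the study 24 hours after the first subject has started".
- **ICU transfer (3.5; Table 1, note d).** Transferred patients are followed for safety and count as having reached a study endpoint. ICU admission is a recorded outcome.
- **Human experience by this route (1.2, 9.1.4).** Section 1.2 says that IV dosing was not tested in the hereditary angioedema clinical package. Section 9.1.4 says: "Pharmacokinetic properties and information about safety have only been derived from modelling and simulation". Section 4.3 reports IV infusion studies in monkeys.

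**The concern.** Waiving SAE reports for an event that is also a disease outcome is common and is not the error. The error is that the waiver is unconditional in a trial where the safety of the IV route is a primary objective (1.3).

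Section 4.3 names hypersensitivity as an important identified risk. Patients enter with a saturation below 90% off oxygen and/or a need for at least 3 L/min (3.2). A serious reaction in such a patient could present as respiratory insufficiency leading to ICU admission, and could look like progression of COVID-19. The waiver as worded covers that case even when the investigator suspects the drug.

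What is at stake is prompt review. The trial runs in five hospitals with staggered early entry, and section 3.7 asks for an evaluation before the next subject is treated. That evaluation depends on other sites hearing of the event quickly.

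**Working it through.** The plan gives no figure to reproduce on this point. The check follows one event through the protocol, then sizes the background.

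**Tracing the event.** Take a patient who is transferred to the ICU with respiratory insufficiency after an infusion, and an investigator who suspects lanadelumab.

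1. *SAE list, hospitalisation criterion.* The event prolongs hospitalisation, but the attached clause says it is not reported as an SAE.
2. *SAE list, other criteria.* The event may also be life-threatening or an important medical event, and these criteria have no waiver. If the clause limits only its own criterion, the event is reportable. If its words are taken at face value, it is not. The protocol does not say which prevails, so one event can be both reportable and exempt.
3. *Ordinary AE.* At grade 2 or higher with suspected causality the event is recorded, but with no expedited reporting and no automatic alert.
4. *SUSAR.* The route requires seriousness. The waiver says the admission is not reported as an SAE; it does not say that the event is not serious. The route is not clearly closed, but a site applying the waiver may not open it.
5. *Cross-site notice.* The 24-hour report and the automatic Castor e-mail both depend on an SAE report. Without one, the protocol describes no other automatic notice.
6. *Stopping rule.* Section 3.7 turns on a severe adverse event attributable to lanadelumab and does not mention an SAE report. An investigator who attributes the event can invoke the rule directly. The term severe is not defined there, and sections 3.7 and 6.3 should be reconciled on whether it means severe or serious.

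The literal reading therefore loses speed and central visibility. It does not remove the recording of suspected events or the stopping rule.

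**Sizing the background.** Inputs:

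- ICU rate p: section 3.1 says of hospitalised COVID-19 patients that "out of these patients about 20% is admitted to the ICU". This covers any cause and is not specific to the trial population, so its use here is an assumption. The range taken is 10% to 30%.
- Treated patients n = 20 (5.3).

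Formulas: expected admissions = n × p; P(at least one) = 1 − (1 − p)^n.

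| p | Expected among 20 treated | P(at least one of 20) |
|---|---|---|
| 10% | 20 × 0.10 = 2 | 1 − 0.9^20 = 0.878 |
| 20% | 20 × 0.20 = 4 | 1 − 0.8^20 = 0.988 |
| 30% | 20 × 0.30 = 6 | 1 − 0.7^20 = 0.999 |

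Across both arms at 20% the expected number is 40 × 0.20 = 8. At any given all-cause rate, the respiratory admissions that the waiver covers can be no more than these.

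**The case against.** The strongest reply is that the clause is part of a single criterion. Death, life-threatening events and important medical events stand beside it without any waiver. An infusion or hypersensitivity reaction severe enough for intensive care would usually meet one of them. On that reading the reaction is reported as an SAE, and the clause removes only ordinary progression. This reading is reasonable, and a reader who inferred that such events can never enter the SAE route would go beyond the text. What remains is that the wording does not say which reading holds, and five sites may read it differently.

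A reader might also infer that the waiver disables the stopping rule. The protocol does not support that. Section 3.7 is triggered by attribution and severity, and entry of the third to fifth participants depends on the second receiving the first dose without severe complications. Neither refers to SAE status. Separately, the temporary-halt provision in 6.3 lets the sponsor suspend the study on safety grounds. The possible loss is timeliness of notice between sites.

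A third reply is that ICU admissions are already captured, through follow-up for safety (3.5) and as an outcome (Table 1). That stands, so adding a by-arm tabulation to the protocol would bring little. But collecting an outcome is not the same as a prompt causality review.

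Finally, the 20% figure describes background disease. That is correct, and it limits what the arithmetic can show.

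**Conclusion.** The point holds in a limited form. Section 6.3 exempts every ICU admission for respiratory insufficiency from SAE reporting, without an exception for suspected drug relation. It leaves open whether the exemption overrides the life-threatening and important-medical-event criteria. Applied literally, it could leave a suspected serious reaction as an ordinary AE and delay the evaluation required by section 3.7.

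The expected 4 admissions among 20 treated patients (2 to 6 over the assumed range) and the 0.988 chance of at least one might be read as the frequency of missed drug reactions. They are not. They count all-cause ICU admissions at a rate quoted for hospitalised patients in general, and they say nothing about how often lanadelumab causes harm. They show only that the exempt type of event is likely to occur, so that a drug-related case could be hidden among background cases.

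The conclusion rests on the protocol wording alone, and on no other provision in it restoring reporting for suspected cases; none was found. The change is worth making because IV safety is a primary objective and human experience by this route is so thin, but it is a clarification of a reporting rule and does not mean that safety oversight is absent.

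**What to change.** In section 6.3:

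1. Limit the waiver to ICU admissions for respiratory insufficiency that the investigator judges to be COVID-19 progression and does not suspect to be related to study drug.
2. State that the other SAE criteria still apply to such admissions, including the life-threatening and important-medical-event criteria.
3. For each ICU admission, record onset time relative to the last infusion, where one was given.

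The AE, SAE and SUSAR text in 6.3 should then be read against 3.5 and 3.7 so that the terms agree. The change concerns reporting only and leaves treatment untouched. It costs a short revision of one clause, one CRF field and a few extra SAE reports.

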***Suspected unexpected serious adverse reactions (SUSARs)***

Adverse reactions are all untoward and unintended responses to an investigational product related to any dose administered.

Unexpected adverse reactions are SUSARs if the following three conditions are met:

1. the event must be serious;
2. there must be a certain degree of probability that the event is a harmful and an undesirable reaction to the medicinal product under investigation, regardless of the administered dose;
3. the adverse reaction must be unexpected, that is to say, the nature and severity of the adverse reaction are not in agreement with the product information as recorded in:
  - Summary of Product Characteristics (SPC) for an authorised medicinal product;
  - Investigator's Brochure for an unauthorised medicinal product.

The investigator in a participating centre will report the SUSAR to the coordinating investigator.

The coordinating investigator will report expedited the following SUSARs through the web portal *ToetsingOnline* to the METC:

- SUSARs that have arisen in the clinical trial that was assessed by the METC;
- SUSARs that have arisen in other clinical trials of the same sponsor and with the same medicinal product, and that could have consequences for the safety of the subjects involved in the clinical trial that was assessed by the METC.

The remaining SUSARs are recorded in an overview list (line-listing) that will be submitted once every half year to the METC. This line-listing provides an overview of all SUSARs from the study medicine, accompanied by a brief report highlighting the main points of concern.

The expedited reporting of SUSARs through the web portal Eudravigilance or ToetsingOnline is sufficient as notification to the competent authority.

The sponsor will report expedited all SUSARs to the competent authorities in other Member States, according to the requirements of the Member States.

The expedited reporting will occur not later than 15 days after the sponsor has first knowledge of the adverse reactions. For fatal or life threatening cases the term will be maximal 7 days for a preliminary report with another 8 days for completion of the report.

**For individual sites, the local investigator completes the SAE report in Castor and providing as much detailed information as known and relevant to the event within 24 hours of discovery of the event.**

**The coordinating investigator will automatically be notified via Castor by email when a new SAE is reported in Castor. If there are technical issues with Castor the local investigator completes the SAE report on paper. A template of this report will be provided in de ISF. The sponsor will report all SAEs using the CCMO module 'ToetsingOnline' to the accredited METC that approved the protocol. By means of this website notifications will be sent to the relevant authorities (METC/LAREB/EudraVigilance). The reporting will occur within 15 days after the investigator has first received information on the SAE. For fatal or life-threatening cases a preliminary report will be offered within 7 days followed by a complete report within 8 days. SUSARs will be electronically reported via ToetsingOnline and the trial coordinator will communicate all SUSARs to the independent monitor of this study.**

## **7. Data analysis**

### **7.1 Sampling design and sample size justification**

This is pragmatic study to deliver a proof of concept on the use of lanadelumab in COVID patients on the ward. No formal sample size has been performed.

### **7.2 Data collection and data management**

All data obtained in the study described in this protocol will be anonymously recorded on CRFs by health professionals who are involved with the treatment of the subjects.

### **7.3 Statistical analysis**

Statistical analysis will be performed using descriptive statistics for tabulation of population as well as results. [name] from our department of health evidence will help with the statistical analysis. Appropriate test will be deployed.

For the primary endpoint we intend to collect repeated measurements of oxygen use in L/min and therefore any significant decline in a patient's health should be reflected in these repeated measurements. We acknowledge that missing data due to death is a potential source of bias, particularly if oxygen is stopped at the point where a significant decline is observed. Therefore, a worst-case scenario sensitivity analysis, in which the highest value of oxygen recorded for any patient is imputed for patients with missing data following their death. Other valid methods to account for missing data due to death will be investigated and included in the Statistical Analysis Plan.

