### Data and outcome variables:

Data on clinical parameters including respiratory rate, oxygen saturation, and supplemental oxygen are registered before and after administration of lanadelumab and then daily. Changes in oxygen support requirement and clinical symptoms are recorded. Laboratory tests are performed during the study: hemocytometry, WBC differentiation, D-dimer, ferritin, CRP, and albumin (Table 1).

Kinins, biomarkers, and functional immunological profiling will be assessed in the forty randomized patients with EDTA plasma (10ml), PBMCs (20ml EDTA), mass spectrometry (2ml blood in specialized medium tube), and citrate plasma (8ml), with a total volume of 40ml per in depth sampling.

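### The worst-case imputation for deaths starts only after death, so it misses readings taken between the stop of oxygen and death, the case Section 7.3 itself names

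*Protocol*

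**What the plan says.** Protocol Section 7.3 defines the endpoint data: "For the primary endpoint we intend to collect repeated measurements of oxygen use in L/min". It infers that "any significant decline in a patient's health should be reflected in these repeated measurements". It then accepts that data missing because of death may cause bias, "particularly if oxygen is stopped at the point where a significant decline is observed".

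The response opens with "Therefore, a worst-case scenario sensitivity analysis". The rule laid down for this analysis reads: "the highest value of oxygen recorded for any patient is imputed for patients with missing data following their death". The section closes by deferring further work: "Other valid methods to account for missing data due to death will be investigated and included in the Statistical Analysis Plan".

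On timing, the paragraph on data and outcome variables in Section 6.1 says that respiratory rate, saturation and "supplemental oxygen are registered before and after administration of lanadelumab and then daily". Table 1 also schedules oxygen need every day, and its footnote d ties that measure to a saturation target above 94%. Section 3.5 treats transfer to the ICU as reaching a study endpoint. Section 5.3 sets 20 participants per group.

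**The concern.** The reason given for the rule and the reach of the rule do not match. The feared event is the stop of oxygen in a patient who is getting worse. The rule starts at a later event, death. Between the two lies an interval in which daily readings are due, and a reading taken there is neither missing nor after death.

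On a scale of oxygen use, a patient from whom oxygen has been withdrawn presumably reads 0 L/min. A patient weaned to room air reads the same, and Section 1.2 reports that state as a good outcome in the icatibant pilot. The statement that decline should show in the repeated measurements therefore fails at the very readings where Section 7.3 expects trouble. The sensitivity analysis is there to show how far deaths could distort the result, but it carries these favourable values through unchanged. The further methods deferred to the SAP are also described as methods for data missing because of death, so nothing in the section points the SAP to this interval.

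**Working it through.** **The rule against its target case**

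| Time in a ward patient who dies | Status of the reading | Does the Section 7.3 rule act? |
|---|---|---|
| Before oxygen is stopped | observed | no, and none is needed |
| After the stop, before death, reading taken | observed, presumably 0 L/min | no: it is not missing |
| After the stop, before death, nothing recorded | missing, but before death | no, on the literal wording |
| After death | missing | yes |

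The protocol gives no figure to reproduce here, so the size is shown on one assumed patient.

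**Inputs.** From the protocol: daily readings (Section 6.1) and 20 per arm (Section 5.3). Assumed: 14 daily readings; 6, 8, 10, 10, 10 L/min (sum 44) before the stop; then k daily readings of 0 before death, with k from 0 to 3; highest value recorded for any patient M = 10 or 15 L/min.

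**Formulas for the patient's mean**
- Available data, no rule: 44/(5 + k)
- Rule as written, M only after death: (44 + (9 − k)M)/14
- M from the stop of oxygen: (44 + 9M)/14
- Rule as written minus M from the stop: −kM/14 for the patient, so −kM/(14 × 20) = −kM/280 for the arm mean

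| M | k | Available data | Rule as written | M from the stop | Arm mean lowered by |
|---|---|---|---|---|---|
| 10 | 0 | 8.80 | 9.57 | 9.57 | 0 |
| 10 | 1 | 7.33 | 8.86 | 9.57 | 0.036 |
| 10 | 2 | 6.29 | 8.14 | 9.57 | 0.071 |
| 10 | 3 | 5.50 | 7.43 | 9.57 | 0.107 |
| 15 | 0 | 8.80 | 12.79 | 12.79 | 0 |
| 15 | 1 | 7.33 | 11.71 | 12.79 | 0.054 |
| 15 | 2 | 6.29 | 10.64 | 12.79 | 0.107 |
| 15 | 3 | 5.50 | 9.57 | 12.79 | 0.161 |

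For example, with M = 15 and k = 1: (44 + 8 × 15)/14 = 164/14 = 11.71, against (44 + 9 × 15)/14 = 179/14 = 12.79. The gap is 15/14 = 1.07 L/min for the patient and 1.07/20 = 0.054 for the arm.

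**On one zero day** the arm mean is lower by M/20, which is 0.50 (M = 10) or 0.75 L/min (M = 15).

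**With no rule at all** the patient's mean falls as k grows (8.80, 7.33, 6.29, 5.50), so a longer interval between stop and death looks better. The last recorded change is 0 − 6 = −6 L/min, the same as for a patient who started at 6 and was weaned.

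**If nothing is recorded in the interval**, the k readings stay empty. With M = 15 and k = 3 the patient's mean over the 11 filled days is (44 + 6 × 15)/11 = 134/11 = 12.18, against 12.79. That is (12.79 − 12.18)/20, or about 0.03 L/min on the arm mean. The gap in the rule remains, but it matters less.

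**The case against.** The strongest reply is that the wording is loose rather than the method wrong. The oxygen-stop case appears in a sentence about missing data, so the reference to death could identify which patients are imputed rather than when imputation starts. No passage says what is recorded once oxygen is withdrawn, so 0 L/min is an inference. Footnote d of Table 1 links oxygen need to a saturation target, and saturation is collected daily, so a zero in a patient below target can be told apart from a weaned zero. ICU transfers have already reached a study endpoint, which leaves only deaths on the ward. An SAP that is not at hand may settle the matter.

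Most of this limits the size rather than removing the gap. Even on the generous reading, a recorded 0 is not a missing value, so the rule does not replace it. Footnote d supplies a means of spotting these zeros, but Section 7.3 analyses oxygen use and does not say to exclude them. The SAP could close the gap, but the methods deferred to it are described in the same limited terms.

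A reader might go further and infer that excess deaths in one arm would be hidden, for instance because a last-value comparison scores such deaths as recoveries, or because each adds 1/20 = 5 percentage points to the share with a fall of at least 3 L/min. The protocol does not support that. It specifies no last-value analysis, no responder endpoint (the 3 L/min figure describes the pilot at 24 hours) and no named repeated-measures model. It gives no expected number of deaths, and nothing on how many would follow a stop of oxygen.

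**Conclusion.** The point holds in a limited form. Section 7.3 sets a rule for a bias that it describes, and the rule starts too late to cover the case described. This follows from the text alone and depends on no assumed number.

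The effect on the sensitivity analysis is small: 0.04 to 0.16 L/min on the 14-day mean of a 20-patient arm for each such patient, and 0.50 to 0.75 L/min on a single zero day. These figures assume recorded zeros, one to three of them, and a maximum of 10 to 15 L/min. The effect is nil if death comes before the next daily reading, and smaller if nothing is recorded after the stop. Under the rule as written such a patient still averages well above a recovered one (11.71 L/min for M = 15, k = 1), so the analysis is weakened, not defeated. In the main analysis, where the protocol shown gives no handling of deaths, the same zeros would count as improvement if used as recorded. How much that matters cannot be stated without the method.

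**What to change.** In Section 7.3, have the worst-case value start when oxygen is stopped without the saturation target being met on room air and death follows, instead of only after death. Add that zeros recorded in that interval are not treated as improvement in the main analysis. Identify them from the saturation already registered each day, or from a CRF field giving the reason for each 0 L/min (weaned, or stopped for another reason).

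The cost is a sentence or two in the protocol or SAP and, if chosen, one CRF field. No extra patients, visits or samples are needed. A worst-rank score for deaths could be among the further methods in the SAP, but it is not needed to close this gap: it would express the effect in ranks rather than litres and is a separate choice of estimand. The change concerns how readings are scored and has no bearing on when oxygen is given or stopped.
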